# PRIMA: randomized prospective multicenter non-inferiority study for primary diagnosis of clinically significant *PR*ostate cancer by PSA and MR *IMA*ging—study protocol for a randomized diagnostic accuracy trial

**DOI:** 10.1186/s13063-026-09750-z

**Published:** 2026-04-25

**Keywords:** Prostate cancer, MpMRI, Targeted biopsy, PSA, Diagnostic accuracy, Randomized trial

## Abstract

**Background:**

Diagnostic pathways based on PSA, digital rectal examination (DRE), and systematic biopsy (SB) may miss clinically significant prostate cancer (csPCa) and lead to overdiagnosis of indolent disease. Multiparametric MRI (mpMRI) and MRI-targeted biopsy (TB) improve detection of csPCa; however, the additional diagnostic value of routine SB in biopsy-naïve men with suspicious MRI findings remains controversial.

**Methods:**

PRIMA is a randomized, prospective, multicenter non-inferiority diagnostic accuracy trial in eight German hospitals. Biopsy-naïve men aged 50–75 years with PSA ≥ 3 ng/ml and/or suspicious DRE undergo mpMRI (PI-RADS v2.1, PI-QUAL v2). Men with PI-RADS 4–5 or PI-RADS 3 with PSA density > 0.15 are randomized 1:1 to TB only (Arm A) or TB + SB (Arm B). Persistent PI-RADS 4–5 lesions with negative biopsy undergo MRI in-bore biopsy.

**Outcomes:**

Co-primary endpoints are csPCa (ISUP ≥ 2) detection and detection of clinically insignificant cancer (ISUP 1). Secondary endpoints include patient-reported outcomes (EORTC-QLQ-C30, EPIC-26, VAS), biopsy-related complications, biopsy approach, MRI in-bore yield, AI/radiomics validation and follow-up cancer incidence.

**Sample size:**

One thousand nine hundred eight men were allocated to achieve 1590 analyzable patients (> 80% power; non-inferiority margin δ = 13%).

**Discussion:**

PRIMA will provide high-level evidence whether systematic biopsy can be safely omitted in MRI-positive biopsy-naïve men, potentially reducing diagnostic morbidity and overtreatment.

**Trial registration:**

ClinicalTrials.gov NCT04993508. Registered on 2 December 2022.

**Supplementary Information:**

The online version contains supplementary material available at 10.1186/s13063-026-09750-z.

## Introduction

### Background and rationale {6a}

In the German healthcare context, optimizing diagnostic efficiency is essential due to increasing demand for prostate cancer screening and limited reimbursement for mpMRI. Although MRI-targeted pathways have demonstrated clinical effectiveness, evidence for their cost-effectiveness and scalability in Germany remains limited. PRIMA addresses this gap by evaluating a high-quality, quality-assured MRI pathway that could reduce unnecessary biopsies and downstream treatment costs while maintaining diagnostic accuracy. Prostate cancer (PCa) is the most common solid cancer among men in Germany, with around 75,000 new diagnoses and 15,000 deaths annually, representing 25% of new male malignancies [1]. Classical diagnostic algorithms combining PSA, DRE, and 12-core SB lead to both overdetection of indolent PCa and missed csPCa [2]. Overdiagnosis results in unnecessary treatment, side effects, and psychological burden, whereas underdetection may delay curative therapy. Several prospective studies have demonstrated that TB alone provides similar detection proportions of csPCa compared with SB, while significantly lowering detection of clinically insignificant cancers [3–7]. Nonetheless, other reports suggest that SB still adds incremental diagnostic value [8–13]. The absolute additional yield of SB for csPCa detection has been estimated at 4–5% in two randomized trials and a Cochrane review [8–10], while TB alone may reduce the detection of ISUP grade group 1 cancers by up to 40% [7]. More recent data from the PROBASE trial in younger men (45–55 years) in a screening setting demonstrated that SB identified 26% additional csPCa compared with TB alone, whereas TB contributed only 6% additional csPCa [14]. Screening trials such as STHLM3-MRI [11] and Göteborg-2 [12] provided population-level insights. In STHLM3-MRI, MRI-based pathways reduced unnecessary biopsies and detection of low-grade cancers but would have missed ~1.7 csPCa cases for each avoided ISUP 1 diagnosis [11]. Göteborg-2 demonstrated comparable csPCa detection between TB-only and combined strategies, with fewer insignificant cancers in the TB-only arm (0.6% vs 1.2%), though some intermediate-risk cancers were detected only by SB [12]. Together, these studies highlight that MRI-targeted pathways can safely reduce overtreatment but may risk missing a small proportion of csPCa. Within Germany, mpMRI before biopsy is guideline-recommended [15]. However, the routine addition of SB remains under debate. The PROBASE trial, focusing on younger men (45–55 years), revealed that SB detected 26% additional csPCa compared to TB, suggesting that MRI interpretation and tumor biology may differ with age [16]. Furthermore, the PRIME trial recently demonstrated that bpMRI could suffice in older men (median age 65) [17], whereas PRIMA intentionally uses mpMRI to address potential diagnostic challenges in younger and intermediate-risk groups [18, 19]. Beyond diagnostic accuracy, PRIMA integrates patient-reported outcomes (PROs) to assess procedural burden (VAS) and quality of life (EORTC-QLQ-C30, EPIC-26). These outcomes are essential as biopsy techniques evolve from transrectal to transperineal approaches, potentially reducing infection risk and improving patient experience [13]. Quality assurance (QA) is a major element of PRIMA: all radiology centers are Q2-certified, ensuring compliance with PI-RADS v2.1 [20] and PI-QUAL v2 [21] standards, while urologists must document proficiency in ≥ 100 fusion biopsies. Despite robust international data, most trials have mixed cohorts with prior biopsy history, different MRI protocols, or lacked uniform QA. PRIMA is unique in enrolling exclusively biopsy-naïve men with well-defined MRI risk thresholds (PI-RADS 4/5 or PI-RADS 3 with PSAD > 0.15) and applying a standardized national QA framework. The study therefore aims to generate definitive evidence for or against omission of SB in MRI-positive men within a German healthcare setting.

### Objectives {7}

#### Primary objective

To determine whether MRI/US fusion-guided targeted biopsy (TB) alone is non-inferior to combined targeted plus systematic biopsy (TB + SB) for detecting clinically significant prostate cancer (csPCa; ISUP ≥ 2) in biopsy-naïve men with suspicious mpMRI.

#### Secondary objectives

To evaluate whether TB alone reduces overdetection of clinically insignificant PCa (ISUP 1) compared with TB + SB.To compare patient-reported outcomes (EPIC‑26, EORTC‑QLQ‑C30, VAS) between arms.To assess complication rates, biopsy avoidance due to mpMRI triage, biopsy approach (transrectal vs transperineal), MR in-bore biopsy yield, ISUP ≥ 3 cancers, stability of PI-RADS on follow-up MRI, and bpMRI vs mpMRI performance.To validate AI and radiomics models for PCa detection.

### Trial design {8}

PRIMA is a prospective, randomized (1:1), multicenter, non-inferiority, parallel-group diagnostic accuracy trial comparing TB alone (Arm A) with TB + SB (Arm B). Randomization is stratified by center using a secure web-based randomization module. The study includes exclusively biopsy-naïve men.

## Methods: participants, interventions, and outcomes

This protocol was prepared in accordance with the SPIRIT 2013 guidelines [22]. The completed SPIRIT checklist is provided as Additional file 1.

### Study setting {9}

The University Hospital Düsseldorf and the German Cancer Research Center (DKFZ) coordinate the trial.

Eight study sites in North Rhine-Westphalia, Germany: five university hospitals (Aachen, Cologne, Düsseldorf, Essen, Herne) and three community hospitals (Mönchengladbach, Essen-Mitte, Recklinghausen).

### Eligibility criteria {10}

#### Inclusion criteria

Male, 50–75 yearsPSA ≥ 3 ng/ml and/or abnormal DREBiopsy-naïve Able to provide written informed consent

#### Exclusion criteria

Prior prostate biopsy or known PCaContraindications to MRI (e.g., incompatible implants)Acute prostatitisInability to undergo MRI or biopsy

### Who will take informed consent? {26a}

Informed consent will be obtained by a qualified study physician at the respective participating study site. Only medically trained investigators who are authorized according to national regulations and listed on the site delegation log may conduct the consent process. Participants will receive written and verbal information outlining trial procedures, potential risks and benefits, alternative diagnostic options, confidentiality provisions, and the voluntary nature of participation. Sufficient time will be provided for questions before written consent is documented. Signed consent forms will be stored securely at each site and managed according to Good Clinical Practice (GCP) requirements.

### Additional consent provisions for collection and use of participant data and biological specimens {26b}

The informed consent process includes consent for the scientific use of pseudonymized MRI imaging data and corresponding pathology results generated within the PRIMA trial. These data may be used for future ethically approved research projects related to prostate cancer diagnostics, including radiomics and artificial intelligence model development and validation. No biological specimens or physical biopsy material will be stored or used for secondary research purposes. All secondary analyses will be performed exclusively on double-pseudonymized or anonymized datasets, ensuring that no directly identifying personal information is accessible to researchers at any time.

## Interventions

### Explanation for the choice of comparators {6b}

The comparator arm (TB + SB) reflects the current standard of care recommended in national and international guidelines and widely practiced across Germany and Europe. Systematic biopsy remains routine in biopsy-naïve men because prior evidence suggests a potential incremental diagnostic yield of approximately 4–5% for clinically significant prostate cancer (csPCa) when added to targeted biopsy. Therefore, TB + SB serves as the appropriate control against which the non-inferiority of TB-only can be rigorously evaluated.

### Intervention description {11a}

#### PSA testing

PSA tests will be performed by general practitioners, office-based urologists, or participating study centers. If a confirmed PSA test is elevated (≥ 3 ng/ml), men will be screened for potential study inclusion.

#### Digital rectal examination (DRE)

DRE is not required for study inclusion. However, in case of a suspicious DRE finding, participants may be included even without elevated PSA. DRE can be performed by general practitioners, office-based urologists, or study center urologists.

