#### Secondary outcomes

Patient-reported outcomes (EPIC-26, EORTC-QLQ-C30, VAS)

Measured using validated questionnaires (metric: continuous scores), analyzed as mean changes over time and between groups (aggregation: mean differences), assessed at baseline, 30 days, and 12 months.Biopsy-related complications

Defined as adverse events within 30 days post-biopsy (measure: clinical assessment; metric: categorical/binary), summarized as proportions by study arm, assessed at 30 days post-procedure.Biopsy avoidance due to mpMRI triage

Defined as the proportion of participants not undergoing biopsy due to non-suspicious mpMRI findings (PI-RADS 1–2 or PI-RADS 3 with PSAD ≤ 0.15), reported as proportion, assessed at screening.Diagnostic performance of DRE

Defined as the association between DRE findings and biopsy outcomes (metric: sensitivity, specificity), analyzed cross-sectionally at baseline and biopsy.Biopsy approach (transrectal vs. transperineal)

Compared in terms of pain (VAS score) and infection rates (binary), summarized as mean differences and proportions, assessed within 30 days post-biopsy.MR in-bore biopsy yield

Defined as detection of csPCa in participants undergoing MR in-bore biopsy after negative or ISUP 1 results (metric: binary), reported as proportion, assessed within 3 months post-biopsy.Detection of higher-grade cancer (ISUP ≥ 3)

Defined as presence of ISUP ≥ 3 cancer on histopathology (metric: binary), reported as proportion, assessed at index biopsy.Comparison of bpMRI vs mpMRI

Retrospective comparison of detection performance (metric: paired binary outcomes), analyzed using constrained maximum likelihood methods, assessed at baseline imaging.Change in PI-RADS score

Defined as change in PI-RADS category between baseline and follow-up MRI (metric: ordinal change), reported as proportions of up- or downgrading, assessed at 12 months.Index-lesion-only analysis

Detection of csPCa based on index lesion targeting only (metric: binary), reported as proportion, assessed at index biopsy.AI and radiomics validation

Diagnostic performance of AI-based models (metric: AUC, sensitivity, specificity), analyzed retrospectively, assessed using baseline imaging and biopsy outcomes.

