### Participant timeline {13}

The participant timeline includes screening, enrollment, baseline assessments, randomization, biopsy procedures, and structured follow-up over 12 months. Only men with mpMRI findings of PI-RADS 4–5 or PI-RADS 3 with PSA density > 0.15 proceed to randomization. Follow-up includes standardized complication reporting, patient-reported outcome assessments, and repeat MRI depending on biopsy results (see Fig. 1).

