### Sample size {14}

#### Assessment for eligibility

Men aged 50–75 with PSA elevation (≥ 3 ng/ml) and/or abnormal DRE. To be allocated to trial: *n* = 1908 (including 20% calculated loss). To be analyzed: 477 patients per randomized arm A/B (PI-RADS 4/5 and PI-RADS 3 PSAD > 0.15), resulting in *N* = 2 × 477/0.6 = 1590.

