## Statistical methods

### Statistical methods for primary and secondary outcomes {20a}

The primary analysis will compare the detection proportion of clinically significant prostate cancer (csPCa; ISUP ≥ 2) between Arm A (TB only) and Arm B (TB + SB) using a non-inferiority framework. Non-inferiority for csPCa detection will be assessed based on the absolute difference in detection proportions (π_TB − π_TB + SB), evaluated using the likelihood score test by Gart and Nam for binomial parameters at a one-sided α level of 0.05. The non-inferiority margin is δ = 13%. Superiority testing for the secondary co-primary endpoint (detection of clinically insignificant PCa, ISUP 1) will be evaluated based on the ratio of detection proportions (π_TB/π_TB + SB) using a one-sided α level of 0.05. All hypothesis tests apply a fixed global significance level of *α* = 0.05.

Secondary outcomes—including biopsy-related complications, biopsy avoidance, diagnostic performance measures, and biopsy approach comparisons—are defined in the Outcomes section according to domain, measurement, metric, method of aggregation, and timepoint. Biopsy-related complications will be summarized as proportions by study arm at 30 days post-procedure. Biopsy avoidance will be reported as the proportion of participants not undergoing biopsy following mpMRI triage at screening. Diagnostic performance outcomes (e.g., DRE, bpMRI vs mpMRI) will be evaluated using standard accuracy measures (e.g., sensitivity, specificity) where applicable.

All detection outcomes are defined as proportions (number of participants with the outcome divided by the number of participants undergoing biopsy in the respective arm). Secondary outcomes will be analyzed descriptively and, where appropriate, using inferential statistical methods.

Patient-reported outcomes (EPIC-26, EORTC-QLQ-C30, VAS) will be analyzed using mixed models for repeated measures (MMRM), including treatment arm, timepoint, and baseline values as covariates.

A detailed statistical analysis plan (SAP) will be finalized and archived prior to database lock and prior to any unblinded analyses.

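### Men with PSA below 3 enter only on a suspicious DRE, so pooling them into the DRE accuracy outcome biases sensitivity upward and specificity downward, by an amount the protocol cannot fix

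*Protocol article*

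**What the plan says.** Four parts of the protocol article bear on this.

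- **Entry.** The inclusion criteria accept a raised PSA, an abnormal DRE, or both. The PSA testing section makes PSA sufficient alone: "If a confirmed PSA test is elevated (≥ 3 ng/ml), men will be screened for potential study inclusion". The DRE section says "DRE is not required for study inclusion" but adds that "in case of a suspicious DRE finding, participants may be included even without elevated PSA".
- **Outcome.** Under Secondary outcomes, the diagnostic performance of DRE is "Defined as the association between DRE findings and biopsy outcomes (metric: sensitivity, specificity), analyzed cross-sectionally at baseline and biopsy". No analysis population or entry route is named.
- **Analysis.** Section {20a} refers back to the Outcomes section for the definition of secondary outcomes, and then says: "Diagnostic performance outcomes (e.g., DRE, bpMRI vs mpMRI) will be evaluated using standard accuracy measures (e.g., sensitivity, specificity) where applicable".
- **Reference standard.** Biopsy follows MRI triage: "Only men with mpMRI findings of PI-RADS 4–5 or PI-RADS 3 with PSA density > 0.15 proceed to randomization".

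**The concern.** Sensitivity and specificity need both DRE-positive and DRE-negative men. Among men with PSA of at least 3 ng/ml the entry rule admits both. Below 3 ng/ml it admits only DRE-positives, so that group can supply true positives and false positives but no false negatives or true negatives. DRE would then be assessed in a sample chosen partly on its own positive result.

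This differs from the partial verification caused by MRI triage. It arises at enrolment and would remain if every enrolled man were biopsied.

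At stake is one prespecified secondary outcome. The published DRE accuracy would depend partly on how many men happened to be referred on DRE alone, and so would not carry over to settings with other referral habits.

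**Working it through.** **Inputs from the protocol.** The entry rule and outcome definition are as above. For scale, the Sample size section gives "To be analyzed: 477 patients per randomized arm A/B", so 2 × 477 = 954 biopsied men, with expected csPCa prevalence of 50%, so 477 with and 477 without csPCa. The protocol states no figure for DRE accuracy or for the share entering on DRE alone, so there is no planned DRE figure to reproduce.

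**Assumptions.** The target condition is csPCa (the outcome says only biopsy outcomes). DRE sensitivity Se, specificity Sp, the share s of DRE-only entrants among biopsied men with a DRE, and their csPCa rate are all assumed.

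**Direction.** Let D1 and D0 be the PSA-eligible men with and without csPCa, and d1 and d0 the DRE-only entrants with and without csPCa.

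- Pooled sensitivity = (D1·Se + d1)/(D1 + d1). The change from Se is d1(1 − Se)/(D1 + d1), which is positive whenever d1 > 0 and Se < 1.
- Pooled specificity = D0·Sp/(D0 + d0). The change from Sp is −d0·Sp/(D0 + d0), which is negative whenever d0 > 0 and Sp > 0.

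The direction is the same against all MRI-positive men, because the men never enrolled (PSA below 3, DRE normal) could add only false negatives and true negatives.

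**Size with equal csPCa rates.** The formulas reduce to s + (1 − s)Se and (1 − s)Sp. With Se = 30% and Sp = 85%:

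| s | Pooled sensitivity | Shift | Pooled specificity | Shift |
|---|---|---|---|---|
| 2% | 0.02 + 0.98 × 0.30 = 31.4% | +1.4 | 0.98 × 0.85 = 83.3% | −1.7 |
| 5% | 0.05 + 0.95 × 0.30 = 33.5% | +3.5 | 0.95 × 0.85 = 80.75% | −4.25 |
| 10% | 0.10 + 0.90 × 0.30 = 37.0% | +7.0 | 0.90 × 0.85 = 76.5% | −8.5 |

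**Size with unequal csPCa rates.** Take 954 men, 50% csPCa in PSA-eligible men, and 30% to 50% csPCa in DRE-only entrants.

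| Assumed Se / Sp | s = 5% | s = 10% |
|---|---|---|
| 30% / 90% | 32–34% / 84–86% | 34–37% / 78–81% |
| 50% / 80% | 52–53% / 75–76% | 53–55% / 69–72% |

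One cell in full, for s = 10%, Se 30%, Sp 90% and 30% csPCa in DRE-only men: 858.6 PSA-eligible men give D1 = D0 = 429.3, and 95.4 DRE-only men give d1 = 28.62 and d0 = 66.78. Sensitivity is (128.79 + 28.62)/457.92 = 34.4%. Specificity is 386.37/496.08 = 77.9%.

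**Against sampling error.** With 477 men in each group, all with a DRE, the 95% half-widths are 1.96 × √(0.30 × 0.70/477) = 4.1 points for sensitivity and 1.96 × √(0.85 × 0.15/477) = 3.2 points for specificity. At s = 2% both shifts fall inside these limits. At s = 5% sensitivity (3.5) does but specificity (4.25) does not. At s = 10% neither does.

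**The case against.** The strongest reply is that nothing in the article says the two entry groups will be pooled. The outcome is a one-line definition, accuracy measures are to be used only where applicable, and a detailed SAP is still to come. The analysis set for one descriptive secondary outcome could be settled there. Entry route can also be derived from baseline PSA and DRE, so nothing is lost by waiting, and the data collection forms are not shown.

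Part of this stands. The restriction needs no change to trial conduct, and it cannot be claimed that the data forms lack an entry-route field. It does not remove the point, because section {20a} sends the reader to the Outcomes section for the definition, and that definition carries no restriction. A stated entry rule and a stated metric do not fit together, which is more than an omitted detail.

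It is also fair that the outcome is minor. It is one of eleven secondary outcomes, does not appear among the listed objectives, and has no hypothesis or power attached.

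A reader might infer that the distortion is large, for instance 40% in relative terms. That figure needs an assumed sensitivity of 20% with a 10% share (0.10 + 0.90 × 0.20 = 28%), which is 8 points. The documents support neither value.

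**Conclusion.** The point holds as a bias of known direction and unknown size in one secondary outcome. If the definition is followed as written, DRE sensitivity is overstated and specificity understated. Under Se 30%, Sp 85% and equal csPCa rates, the shift runs from 1 to 2 points at a 2% share of DRE-only entrants to 7 to 9 points at 10%. At small shares it may lie within sampling error. The size depends on three unknowns: the share, those men's csPCa rate, and the DRE's own accuracy. The share alone does not set it. Because DRE is optional for PSA-eligible men but always present in DRE-only entrants, the share among men with a DRE result may exceed the share among all enrolled men.

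Two stronger readings are not supported. The first is that the main result is compromised: the co-primary endpoints, sample size and randomized comparison do not use the DRE result. The second is that excluding DRE-only entrants would recover the DRE's true performance: only MRI-positive men are biopsied and DRE is optional, so partial verification and possibly selective recording remain.

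**What to change.** In the Secondary outcomes entry on DRE performance:

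1. Restrict sensitivity and specificity to biopsied men with PSA of at least 3 ng/ml and a recorded DRE.
2. Report men who entered on DRE alone separately, as a positive predictive value only.
3. State that all these estimates apply to MRI-positive, biopsied men, and give the number of PSA-eligible men without a DRE result.

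Entry route (PSA, DRE or both) should be identifiable in the dataset. It follows from baseline PSA and DRE if both are captured.

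The cost is a sentence or two in the outcome definition and a slightly smaller denominator. Eligibility and procedures do not change. The Trial status section reports no participants enrolled at submission, so the definition can be settled before data accrue.
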